### Analysis population and missing data

Participant data will be analysed on an intention-to-treat (ITT) basis as per group allocation. Any missing repetitions from the prescribed number of repetitions will be interpreted as non-compliance. Mean values of data until the point of drop out will be imputed for the remaining intervention for participants who drop out. If the participant has not made a single repetition, the group mean value will be imputed for this participant.

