**Fig. 3 Fig3:**
[figure not shown]
Hip extension. The subject provided consent to appear

**Table 1 Tab1:** Exercise descriptors

	Knee extension (Fig. 1)	Hip abduction (Fig. 2)	Hip extension (Fig. 3)
1. Load magnitude	10-12 RM	10-12 RM	10-12 RM
2. Number of repetitions	10	10	10
3. Number of sets	3	3	3
4. Rest in between sets	1 min 50 seconds	1 min 50 seconds	1 min 50 seconds
5. Number of exercise interventions (per (day) or week)	3/week	3/week	3/week
6. Duration of the experimental period ((day) or weeks)	6 weeks	6 weeks	6 weeks
7. Fractional and temporal distribution of the contraction modes per repetition and duration (s) of one repetition	3 s concentric	3 s concentric	3 s concentric
	2 s isometric	2 s isometric	2 s isometric
	3 s eccentric	3 s eccentric	3 s eccentric
8. Rest in-between repetitions ((s) or (min))	No	No	No
9. TUT ((s) or (min))	8 s/repetition	8 s/repetition	8 s/repetition
	80s/set	80s/set	80s/set
	4320 s/total intervention	4320 s/total intervention	4320 s/total intervention
10. Volitional muscular failure	Yes	Yes	Yes
11. Range of motion	90° to 180^o^	0° to 45^o^	45° hip flexion to 0° hip flexion/extension
12. Recovery time in-between exercise sessions ((h) or (d))	48 h	48 h	48 h
13. Anatomical definition of the exercise (exercise form)	Knee extension is performed with the participant sitting in 90^0^ knee flexion. The elastic band is looped around the ankle and around a solid anchor near the floor under the participant (Fig. 1). The knee is extended to approximately 180^0^.	Hip abduction will be performed in standing with the elastic band looped around the ankle and anchored to the wall at ankle height. The stance leg will be in front of the band and the target hip in a slight internal rotation (Fig. 2). Hip abduction will then be performed to approximately 45^0^.	Hip extension will be performed in standing with target hip in 45^0^ hip flexion. One end of the elastic band fixated at knee height and looped around the back of the knee (Fig. 3). The hip is then extended to approximately 0° hip extension whilst maintaining a neutral lumbo-pelvic position.

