Participants will receive an elastic band, a BandCizer™ and an iPad with the BandCizer™-app. Before and after each exercise they are instructed to record their knee pain on a 100 mm VAS that is integrated in the app. They are instructed to perform the exercises three times each week during the 6-week intervention. Twice a week the exercises are performed at home whilst the last exercise session will be a group training session supervised by a physiotherapist. In connection with the initial instruction of the exercises, 10-12 RM will be determined by shortening the elastic band to a length where the participants feel that they will not be able to perform more than 10 repetitions. The pulling force exerted when the exercise is performed correctly will be measured by the BandCizer™ and recorded by the investigator. If the participants become able to perform more than 10 repetitions during the intervention period, they will be instructed to shorten the band or change to a different grade of band. In this situation a new measurement of recommended pulling force will be made.

The feedback group will have access to live visual and auditory feedback on TUT and pulling force from the BandCizer™-app when they perform the exercises. Controls will only receive visual feedback on pulling force.

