### Withdrawal and adverse events

If a participant experiences an adverse event (e.g. an injury to the musculoskeletal system such as a muscle tear, a muscle strain, a sprained joint, injury from falling, DOMS that lasts for more than 48 h after performing the exercises or exacerbation of PFP) and is not able to perform the exercises, the participant will be able to withdraw from the study. The study may also be discontinued by participant request or withdrawal of informed consent. Data until the point of withdrawal will be included in the data analyses. If a participant experiences an adverse event and has to withdraw, data until the last training before the adverse event occurred will be included in the analyses. The participants are instructed to report any adverse events to the primary investigator as quickly as possible either by e-mail, SMS, phone call or during the supervised training sessions. The primary investigator will then ask the participant if the event occurred when they performed the exercises or during other activities. If the event occurred during the exercises the primary investigator will report the incident to the sponsor as quickly as possible and no later than 15 days after the participant reported the event. Sponsor will report adverse events to the Ethics Committee of North Denmark Region no later than 7 days after being informed.

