### Data collection and management

All data will initially be written on paper forms and afterwards entered into Microsoft Excel 2013 (Microsoft Corporation, Washington, USA) by the primary investigator at the study site where data originated. Data from BandCizer™ is uploaded from the iPad to an online server from where raw data on TUT, pulling force, repetitions and pain will be accessible only for the primary investigator. A visualisation of the data output from BandCizer™ is seen in Fig. 6. Prior to the statistical analyses data will be exported to IBM SPSS Statistics ver. 23 (IBM, New York, USA). Participants will complete all self-report data forms. All original paper forms and informed consent forms will be kept in a locked cabinet at the study site. All data will be kept for 10 years after completion of the study which in accordance with The European Code of Conduct for Research Integrity [32].

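### For participants who stay in the trial, the missing-repetition rule does not separate lost sensor data from exercise not done

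*Protocol article*

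**What the plan says.** The rule stands in the protocol article under Analysis population and missing data: "Any missing repetitions from the prescribed number of repetitions will be interpreted as non-compliance". Two exceptions follow it. For drop-outs, "Mean values of data until the point of drop out will be imputed for the remaining intervention for participants who drop out". For a participant with nothing at all, "If the participant has not made a single repetition, the group mean value will be imputed for this participant". The section Withdrawal and adverse events adds that, after withdrawal for an adverse event, "data until the last training before the adverse event occurred will be included in the analyses".

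On the source of the counts, Data collection and management says: "Data from BandCizer™ is uploaded from the iPad to an online server". It lists repetitions among the raw data obtained by that route.

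On the sessions, the Intervention section says: "Twice a week the exercises are performed at home whilst the last exercise session will be a group training session supervised by a physiotherapist". The prescribed number therefore includes sessions at which a professional sees the participant train.

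Total repetitions is a secondary outcome (Outcomes), compared between arms with an unpaired t-test (Statistical analysis). The same section plans exploratory correlations of pain with compliance and of total dose with strength gain.

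**The concern.** A repetition can be absent from the data because it was not performed, or because it was performed and the sensor, iPad or upload failed. The first is non-compliance. The second is missing data. The rule puts both in the first class for anyone still in the trial.

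The clearest case is a weekly group session: the participant trains in front of the physiotherapist, the recording fails, and the session is scored as not done against direct evidence.

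At stake are total repetitions, any compliance percentage built on them, and the two exploratory correlations, in which device failure would be read as behaviour. The Strengths section puts objective measurement of compliance first among the design's advantages. The Limitations section considers who or which body part moves the band, but not recordings that are lost.

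**Working it through.** **Inputs**
- Table 1: row "2. Number of repetitions" gives 10; row "3. Number of sets" gives 3; 3 sessions per week for 6 weeks; 8 s per repetition; three exercises.
- Intervention section: two home sessions and one supervised session per week, so 12 and 6 over the trial.
- Rate of lost recordings: not given. The values below are assumptions.
- True completion: not given. 80% is assumed for illustration.

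**Reproducing the plan's own figure**
- Repetitions per exercise: 10 × 3 × 3 × 6 = 540.
- TUT per exercise: 540 × 8 s = 4,320 s, which agrees with Table 1.
- All exercises: 540 × 3 = 1,620 repetitions over 18 sessions, so 1,620 / 18 = 90 per session.

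**Effect of lost sessions on a participant who did everything**

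Scored shortfall = k / 18 for k lost sessions.

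| Lost sessions | Repetitions removed | Scored non-compliance (true value 0%) |
|---|---|---|
| 1 | 90 | 5.6% |
| 2 | 180 | 11.1% |
| 3 | 270 | 16.7% |
| 4 | 360 | 22.2% |

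**Effect at 80% true completion**

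True total = 0.80 × 1,620 = 1,296. Scored total = 1,296 × (1 − f), where f is the fraction of performed repetitions that is lost.

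| f | Scored total | Scored non-compliance (true value 20%) |
|---|---|---|
| 0 | 1,296 | 20.0% |
| 5.6% (1 of 18) | 1,224 | 24.4% |
| 10% | 1,166 | 28.0% |
| 20% | 1,037 | 36.0% |

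**Between arms**
- With the same f in both arms, both means are multiplied by (1 − f), so a true difference shrinks by the fraction f: 5.6% for one session in 18.
- A false difference needs unequal loss. At 80% completion in both arms, a 10% loss in one arm alone would give 1,296 × 0.10 ≈ 130 repetitions. This is a hypothetical case.

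**Where the rule does not reach**

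Take a drop-out after week 3 at 80% completion. The recorded count is 0.80 × 810 = 648. Reading the stated mean imputation as filling in repetition counts gives 648 × 2 = 1,296. Absent repetitions after drop-out are therefore not scored as zero, and the problem is confined to retained participants.

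**An uneven result among retained participants**

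If having made no repetition is judged from the sensor record, a participant whose recordings all failed receives the group mean. One with a single complete recorded session is scored 90 of 1,620.

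**Check of the remedy**

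At 80% completion with one session lost, recorded repetitions over those prescribed in the 17 observed sessions are 1,224 / (17 × 90) = 1,224 / 1,530 = 80.0%, the true value.

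**The case against.** **The rule may concern performance only.** It speaks of a shortfall from the prescribed number, and the next exception is worded in terms of repetitions made. It could be read as silent on device faults, with their handling left to the analysis plan, which is not shown. That plan may well deal with faults. But the published sentence is not silent: it classes any shortfall as non-compliance, and the only described route for counting repetitions is the sensor chain. A plan that follows the sentence inherits the problem, and one that handles faults has to depart from it.

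**The rule is conservative and neutral between arms.** Much of this stands. Both arms use the same sensor, iPad, app and upload route, and the described differences lie in the feedback shown. Equal loss only shrinks a difference in proportion. The level of compliance would still be wrong, and equal loss is presumed, not assured.

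**Exceptions will excuse real non-compliance.** This stands and limits the remedy. The Strengths section cites a study in which self-reported dose was 2.3 times the sensor measure, so later participant accounts of a fault are weak evidence. Pain ratings without repetitions are weak too: someone may enter pain and skip the exercise. They also travel by the same upload, so they would miss upload failures. Attendance does not prove that all 90 repetitions were done.

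**Conclusion.** The point holds for participants who remain in the trial. A performed session whose recording or upload fails is scored as non-compliance, at 90 of 1,620 repetitions (5.6%) if fully performed. Total repetitions and the compliance and dose summaries are too low whenever this happens. How often it happens is unknown, so the figures above are a range over assumed losses and not an estimate.

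A reader might infer more, but the documents do not support it:
- **That every absent repetition is scored as zero.** Drop-outs and participants with no repetitions have means imputed.
- **That some sessions lie outside the sensor's reach.** No session, home or supervised, is described as unrecorded, and no loss is reported.
- **That the primary outcome is distorted.** Scoring an absent repetition as 0 s would add 8 × 2/18 = 0.89 s for two lost sessions in a participant with no true deviation. The text does not say this. The Outcomes section defines the deviation from actual TUT, so a repetition without a TUT does not enter the mean.
- **That the rule creates a false benefit or harm of feedback.** That requires unequal loss, for which there is no evidence.

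This is a correction to secondary and exploratory outcomes. It is worth making before data are seen: the primary investigator opens the allocation envelopes (Randomisation) and alone has access to the raw sensor data (Data collection and management), so any later exception would be made with allocation known.

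**What to change.** Amend the rule so that a session is unobserved, meaning missing and not zero, only in two cases:
1. The participant was seen training at a supervised session, but no recording exists.
2. A sensor, iPad or upload fault was logged at the time and verified by the investigator.

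All other missing repetitions remain non-compliance, and the imputation rules for drop-outs are untouched. Pain ratings alone and retrospective participant reports should not qualify.

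Express repetitions as recorded over prescribed in observed sessions. Report the number of unobserved sessions by arm, and keep the present count, with all missing repetitions as non-compliance, as a sensitivity analysis.

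The cost is a sentence or two in the rule, a short fault and attendance log, and one extra analysis. Group sessions are already scheduled and non-attenders followed up, so attendance is largely known. The downside is that some true shortfall within an excused session may go uncounted; the sensitivity analysis, which credits nothing for those sessions, bounds this.

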### Monitoring

A data monitoring committee will not be established as the intervention uses exercises that are commonly used in the population of interest and do not pose a threat to the participants. This exercise intervention has previously been used for adolescents with this type of knee condition and no adverse effects as a result of the exercise intervention have been reported. It involves exercises that are under the volitional control of the participant. They tolerate it well and there will be no stopping rules planned.

### Access to the final trial data set

The primary investigator and all co-authors will have unlimited access to the final data set before publication. The data, containing the de-identified individual patient data, will be publically available no later than 6 months after publication, consistent with the recent proposal by the International Committee of Medical Journal Editors (ICMJE) [33].

## Discussion

Patellofemoral pain is one of the most frequent knee conditions among adolescents and has a prevalence of 7 % [2, 3]. Treatment seems to be less efficacious in adolescence compared to adulthood [6] and compliance has been shown to play a role, probably because a large proportion of adolescents do not follow their exercise prescription [7]. The XRCISE-AS-INSTRUcted-1 trial will add knowledge as to whether or not visual and auditory feedback on TUT will improve the ability to perform exercises as prescribed.

The specific exercises have been chosen based on a recommendation of strengthening the hip and quadriceps muscles [2, 4]. In addition, activation of the trunk muscles has also been found beneficial in treating PFP [34, 35] and therefore free-standing hip exercises have been chosen to increase trunk activation compared to non-standing hip exercises such as the side-lying hip abduction. In order to be able to measure compliance with the BandCizer™ the participants need to use elastic bands as resistance instead of dumbbells or training machines however, elastic bands provide similar muscle activation as dumbbells [36].

### Strengths

The recruitment and study design has several strengths. Firstly, the use of BandCizer™ provides an objective measure of compliance which was requested in the latest systematic review on self-reported compliance to home-based exercise programs [13]. A recent study showed that adolescents reported a 2.3 times higher exercise dosage in their exercise diary compared to TUT data from the BandCizer™ (Rathleff et al. *in review*)*.* This highlights the importance of an objective measure of compliance. Secondly, the participant blinding of primary outcome measures will ensure that the participants do not focus more on performing the exercises as prescribed than they would when receiving standard exercise prescription by a physiotherapist. Thirdly, the inclusion criteria used in this study are in line with those of previous studies of this patient group [3, 7, 29, 34] which will make comparisons across studies easier. Fourthly, reporting the study protocol using the SPIRIT statement, and outlining the specific exercise descriptors, which has been requested in a recent review on exercise interventions for patients with chronic conditions by Hoffmann et al. [37], facilitates the replication of the study’s findings and its translation into clinical practice. Fifthly, the intervention resembles current physiotherapy practice by combining home-based and supervised training sessions, which increases the external validity.

### Limitations

The participants know that they participate in a study and their exercises are somehow being recorded. This may lead to an increased compliance that does not represent normal clinical practice, however, this limitation will apply to both the feedback group and the controls. The previous study on BandCizer™ and adolescents with PFP by Rathleff et al. (Rathleff et al. *In review*) found a low compliance in spite of the fact that the participants received feedback on pulling force. This emphasises that compliance may not be influenced by using BandCizer™ and receiving feedback on pulling force alone. Another theoretical limitation is that BandCizer™ can only record what is occurring at the exercise band and not who is performing the exercises or if they are being performed with other body parts.

## Conclusion

The objective of The XRCISE-AS-INSTRUcted-1 trial is to determine if live feedback on TUT will improve the ability to perform the exercises as prescribed among adolescents with PFP. This could potentially solve the problem of low compliance in this patient group.

## Abbreviations

DOMS, Delayed Onset Muscle Soreness; GP, General Practice; ICC, Intraclass Correlation Coefficient; ITT, Intention-To-Treat; PFP, Patellofemoral Pain; ROM, Range Of Motion; RR, Relative risk; RM, Repetition Maximum; TUT, Time Under Tension; VAS, Visual Analog Scale
